### Safety, laboratory and imaging assessments

To assure the safety of the study patients a substantial examination program is performed. The patients are under hospital surveillance at least 1 hour prior to infusion and for 24 hours after the start of infusion. Physical examinations are performed at all scheduled visits and vital parameters (e.g. blood pressure, pulse rate, respiratory rate, oxygen-saturation and body temperature) are monitored throughout the infusion time until 24 hours after start of infusion. Moreover, patients are evaluated with regard to clinical signs, symptoms (including AEs) and subjective well-being.

Laboratory parameters for safety analysis and immune monitoring are evaluated at every study visit. Moreover, during treatment, blood will be drawn prior to the start of infusion, at the end of the 6-hour drug infusion period and at 24 after the start of infusion. Blood chemistry parameters include sodium, potassium, calcium, chloride, bilirubin (total), aspartate aminotransferase (AST, or SGOT), alanine aminotransferase (ALT, or SGPT) gamma-glutamyltransferase (GGT), alkaline phosphastase, antithrombin III, albumin, creatinine, uric acid, lactate dehydrogenase, partial thromboplastin time (PTT), quick prothrombin time, fibrinogen and the C-reactive protein (CRP). Hematology parameters encompass hematocrit, hemoglobin (Hb), red blood cell (RBC) count, white blood cell (WBC) count, reticulocytes, platelets and differential WBC. An extensive immune monitoring program determines lymphocyte subsets (CD4, CD8 T cells, B cells, NK cells, monocytes) including effector, central memory as well as regulatory T cells and cytokine release profiles comprising interleukin-2 (IL-2), IL-4, IL-6, IL-8, IL-10, interferon-gamma (IFN-γ), and tumor necrosis factor-alpha (TNF-α). Experimental ELISPOT-analysis to evaluate the induction of tumor specific immune responses after treatment with FBTA05 is restricted to CLL samples.

Bone marrow biopsies are done before the start of treatment, moreover at the EOS and, 12 and 24 months after the start of therapy. Disseminated tumor cells will be determined by analyzing bone marrow aspirates taken from the iliac crest. Changes in the presence of disseminated tumor cells in the bone marrow will be assessed according to NCI criteria.

Tumor assessment via imaging techniques (sonography, compute tomography, magnetic resonance tomography or positron-emission tomography) is clinical practise for the advanced stage of disease and will be performed at the screening, end of study visit and follow up visits scheduled 6, 9, 12 and 24 month after onset of the study. Assessment will be done according to Response Evaluation Criteria in Solid Tumors (RECIST).

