### Previous trials and clinical data

Prior to the start of the current phase I/II dose escalating study, FBTA05 was administered in a compassionate use setting to patients with recurrent and refractory B cell malignancies following allo-SCT, and within a phase I/II trial (IV-A05-LL-01, EudraCT No: 2006-006694-24) to patients with relapsed or refractory CLL in an autologous setting.

In compassionate use a limited number of advanced cancer patients were treated with FBTA05. These, included 4 patients with refractory Chronic Lymphocytic Leukemia (CLL), 4 patients with refractory high-grade non-Hodgkin Lymphoma (HG-NHL) and 1 patient with refractory Acute Lymphocytic Leukemia (ALL) [16]. The treatment comprised escalating doses of FBTA05 with a range of 10–2,000 μg per single infusion. The maximum cumulative dosage administered per patient ranged between 130–13,610 μg of FBTA05. The duration of treatment was between 5–76 days. Following FBTA05 treatment, patients received DLI. Due to the nature of the different indications, the number of peripheral B cells prior to the start of FBTA05 infusions showed a large variation. An anti-tumor response (decrease of leukemic cells and shrinking of lymph nodes) was observed in 3 of 4 CLL patients. In 1 case of HG-NHL, a halt of progression for almost 4 months was observed. The effect of FBTA05 in the other patients was not evaluable due to other concomitant treatment or disease (fungal infection). Relapse finally occurred in all patients. The main side effects were restricted to fever, chills, bone pain and transient increase in γ-glutamyl transpeptidase (γGT). Only one case of GVHD (grade 3) was observed after FBTA05 and DLI and this was in the ALL patient. In context of the administration of the highest cumulative dose of FBTA05 (6,240 μg), a transient granulocytopenia was detected in a HG-NHL patient. The cytokine profile was characterized by a transient increase of IL-6, IL-8 and IL-10. Human anti-mouse antibodies (HAMAs) were not detectable. According to the current experience with the anti HER2/neu directed trAb ertumaxomab there is a correlation between the formation of HAMA and human anti-rat antibodies (HARAs), so HARA development in these patients would seem to be unlikely [17].

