### Primary and secondary endpoints

The primary endpoint in Phase I is the incidence of dose limiting toxicities (DLTs), in phase II the objective response rate. The secondary endpoints are safety and efficacy. Regarding safety, the recommended dose of FBTA05 in combination with DLI for further efficacy studies will be determined. Furthermore, the incidence of adverse events (AEs), the presence of HAMAs after FBTA05 application, the need to discontinue FBTA05 infusion, vital functions, the physical examination findings, laboratory parameters, concomitant medication and as pharmacodynamic endpoints the serum levels of cytokines will be recorded.

In terms of efficacy the clinical benefit rate, the duration of response, the time to progression, the overall survival, the ECOG performance status, the tumor specific response, lymphocyte subsets, activation signs and memory status of T cells will be analysed.

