### Number of patients and eligibility criteria

There will be a maximum of 24 patients in the MTD evaluation part of phase I: 12 patients for CLL / low-grade NHL, 12 patients for high-grade NHL. There will be a maximum of 12 patients in phase II of the study: 6 patients for CLL / low-grade NHL, 6 patients for HG-NHL. A total of maximal 30 patients will be included in the study.

Patients of both genders, any ethnic origin and at least 18 years old are included in the study if they meet the criteria given in Table 2. All participating patients have to sign the written informed consent. Patients can be withdrawn from the study for medical reasons at any time and must be withdrawn in the event of a dose-limiting toxicity. Patients can recall their consent at any time without any negative implications for their further treatment.

**Table 2 T2:** Eligibility criteria of the FBTA05 trial

	
**Inclusion criteria**	- confirmed CLL, low-grade NHL or high-grade NHL
	- CD20 positivity
	- relapsed or refractory disease > 60 days after allogeneic transplantation
	- adequate hematological, liver and kidney functions
	- platelet count ≥ 25 G/l
	- ECOG performance status ≤ 2
	- negative pregnancy test (adequate contraception during study in women of child bearing potential)
**Exclusion criteria**	- anti-CD20 or anti-T cell antibody treatment < 3 months before FBTA05 treatment
	- positivity for human anti-mouse antibodies
	- history of GVHD °III or °IV, or GVHD requiring steroid therapy with ≥ 10 mg / day
	- known hypersensitivity to recombinant murine or rat proteins
	- acute or uncontrolled chronic infections, viral infections at risk of reactivation (e.g. HCV, HBV, HIV)
	- patients unable or unwilling to comply fully with the protocol

*CLL* chronic lymphocytic leukemia, *NHL* Non-Hodgkin's lymphoma, *ECOG* Eastern Cooperative Oncology Group, *HAMA* human anti-mouse antibody, *GVHD* graft versus host disease, *HCV* hepatitis C virus, *HBV* hepatitis B virus, *HIV* human immunodeficiency virus.

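### RECIST is the only standard named for imaging response in a CLL and lymphoma trial with objective response as its phase II primary endpoint, and blood disease has no stated place in response

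*Protocol article*

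**What the plan says.** All references are to the protocol article.

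- **Endpoint.** Primary and secondary endpoints gives the primary endpoint as "in phase II the objective response rate". Duration of response and time to progression are secondary. That section does not define objective response.
- **Population.** Table 2 admits patients with "confirmed CLL, low-grade NHL or high-grade NHL". Study design enrols by disease entity so that differences in drug response between the entities can be examined.
- **Imaging.** Safety, laboratory and imaging assessments describes tumour assessment by sonography, CT, MRI or PET at screening, at the end-of-study visit and at 6, 9, 12 and 24 months, and closes: "Assessment will be done according to Response Evaluation Criteria in Solid Tumors (RECIST".
- **Marrow.** The same section says: "Bone marrow biopsies are done before the start of treatment, moreover at the EOS and, 12 and 24 months after the start of therapy". It adds: "Changes in the presence of disseminated tumor cells in the bone marrow will be assessed according to NCI criteria".
- **Blood.** White cell count, differential and lymphocyte subsets including B cells are collected at every study visit, under the safety laboratory and immune monitoring programmes. Lymphocyte subsets also appear among the secondary efficacy endpoints, as a separate item.
- **Prior experience.** Previous trials and clinical data describes the anti-tumour response in 3 of 4 CLL patients as "decrease of leukemic cells and shrinking of lymph nodes".

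**The concern.** One of the two entities includes a leukemia, whose burden lies partly in the blood. The imaging standard named is, by its own title, meant for solid tumours, and the protocol attaches it to scans. A scan can show the nodal half of the response described in the compassionate-use CLL patients but not the leukemic-cell half.

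If imaging decides who is a responder, two errors are possible. A patient whose leukemic cells clear but whose scans show little to grade is missed. A patient whose nodes shrink while the leukemic count rises is counted as a responder.

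The stake is the phase II primary endpoint in CLL/low-grade NHL, and with it the comparison between entities for which the cohorts are kept separate. A standard that suits one entity less well than the other can create or hide a difference. Duration of response and time to progression use the same classification.

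**Working it through.** **1. The plan's own size figure.** Number of patients and eligibility criteria gives maxima of 24 in phase I, 12 in phase II and 30 in total. Study design counts 2 or 3 patients per entity from the last MTD-level cohort towards phase II.
- Phase I: 4 cohorts × 3 patients × 2 entities = 24.
- Added in phase II, with 3 carried over per entity: 2 × (6 − 3) = 6.
- Total: 24 + 6 = 30, which reproduces the stated figure.

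The ORR denominators are therefore at most 6 per entity and 12 overall. Statistics describes the study as exploratory, so there is no power or target ORR to reproduce.

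**2. What is measured, and against what.**

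| Disease site | Times | Criterion named | Stated link to objective response |
|---|---|---|---|
| Nodes and masses (imaging) | screening, end of study, 6, 9, 12, 24 months | RECIST | none explicit |
| Marrow | baseline, end of study, 12, 24 months | NCI | none explicit |
| Blood (counts, differential, B cells) | every study visit | none | none |

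Two sites have a criterion, and one of these is a solid-tumour standard. Blood has none. Marrow is absent at 6 and 9 months, when imaging is done.

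**3. Weight of one patient.**
- Per entity: 1/6 = 16.7 percentage points.
- Both entities pooled: 1/12 = 8.3 percentage points.
- Example, with exact (Clopper-Pearson) 95% intervals: 2/6 = 33.3% (4.3% to 77.7%) becomes 3/6 = 50.0% (11.8% to 88.2%) when one patient is reclassified.

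The intervals overlap almost entirely, so no formal conclusion turns on one patient. What changes is the reported point estimate.

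**4. How often it might happen (assumption, not in the documents).** Let q be the share of patients whose imaging category would differ from a disease-specific category. The chance that at least one of 6 is affected is 1 − (1 − q)^6.

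| q | Chance of at least 1 of 6 |
|---|---|
| 10% | 1 − 0.9^6 = 47% |
| 20% | 1 − 0.8^6 = 74% |
| 30% | 1 − 0.7^6 = 88% |
| 50% | 1 − 0.5^6 = 98% |

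These figures show sensitivity only. Nothing in the documents fixes q.

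**The case against.** The strongest reply is that the article never says objective response is RECIST alone. The RECIST sentence closes a paragraph that opens: "Tumor assessment via imaging techniques (sonography, compute tomography, magnetic resonance tomography or positron-emission tomography) is clinical practise for the advanced stage of disease". Naming RECIST for scans and NCI criteria for marrow is compatible with a composite definition set out in the full protocol, which is not shown. This stands: ORR by RECIST alone is an inference. The absence of a combination rule from a condensed article is not itself a fault.

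Three stronger readings also fail:

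- **Marrow disease goes unscored.** The text contradicts this, since marrow change is assessed by NCI criteria at fixed times.
- **The evaluable denominator falls below 6 because some patients have no measurable lesion.** Table 2 lists no such entry requirement, but it is plainly abbreviated, and its silence proves little. Statistics defines the efficacy population by treatment received, and no rule removes patients for lack of a lesion.
- **Response is not measured at all in one entity.** That entity combines CLL with low-grade NHL, and shrinking nodes were part of the compassionate-use CLL response. Imaging therefore captures some of it.

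It may also be said that 16.7 points per patient is true of any binary endpoint with 6 patients, and that the study is descriptive. Both are correct. The figure measures the consequence of an error and is no evidence that one occurs. A descriptive rate, however, has no content beyond the classification of each patient.

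What the reply does not remove is the stated choice of a solid-tumour standard for imaging in CLL and lymphoma. A composite definition elsewhere would still take its imaging component from RECIST.

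**Conclusion.** The point holds in a limited form. RECIST is the only standard named for imaging response in a trial with an ORR primary endpoint in CLL and NHL. Blood disease is measured without a stated role in response, contrary to how the compassionate-use CLL responses were described. As written, imaging by RECIST cannot register response or progression in blood, and CLL patients are the most exposed to misclassification.

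Each misclassified patient shifts an entity's ORR by 16.7 points, or the pooled ORR by 8.3. The error can go either way, and the number of patients affected is unknown. The conclusion assumes that the imaging result carries substantial weight in objective response. The article suggests this but does not state it. If the full protocol already uses disease-specific composite criteria, the remaining defect is that the published sentence names the wrong standard.

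The phase I DLT endpoint and the sample size are not affected. The matter should be settled before phase II responses are classified, because it decides who counts as a responder.

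**What to change.** In the imaging paragraph of Safety, laboratory and imaging assessments, replace RECIST as the basis for objective response:

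- For CLL, name NCI-type CLL criteria covering blood, marrow and nodes. For low-grade and high-grade NHL, name lymphoma response criteria.
- In Primary and secondary endpoints, tie objective response, duration of response and time to progression to these criteria.
- At the end-of-study visit and at 12 and 24 months, derive one overall category from blood counts, imaging and marrow.
- At 6 and 9 months, use blood counts and imaging only, and label the category as without marrow confirmation. Marrow is not scheduled then, so a full category at every visit cannot come from existing data.
- Keep RECIST lesion change as a supportive description.

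The cost is a revised response form and slightly more analysis work. One detail needs confirming: laboratory tests are set for every study visit, while the later visits are called post-study follow-up, so the text should make clear that blood counts are taken there. The maxima of 6 per entity, 12 in phase II and 30 in total stay as they are.

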### Statistics

The study is exploratory and is not powered to address any predefined hypotheses. The safety analysis will be performed on the safety analysis set, which includes all patients who received at least one FBTA05 infusion. The efficacy analysis will be performed on both the safety analysis set, which includes all patients who received at least the first three infusions and the first DLI (safety part). Efficacy endpoints will be analyzed by use of appropriate descriptive techniques.

#### Sponsor

Klinikum rechts der Isar (RdI), Technische Universitaet Muenchen (TUM).

### Study approval

Before start of the trial, the trial protocol, informed consent document and any other trial documents were submitted to the independent ethics committee and the regulatory authority (Paul-Ehrlich-Institute, PEI). Ethics approval was granted on 14 January 2010, PEI approval on 16 July 2010.

### Registration

The trial protocol was registered at http://www.clinicaltrials.gov and was given the number NCT01138579.

### Good clinical practice

The procedures set out in this trial protocol, pertaining to the conduct, evaluation and documentation of this trial, are designed to ensure that all persons involved in the trial abide by Good Clinical Practice [20] and the ethical principles described in the current revision of the Declaration of Helsinki [21]. The trial will be carried out in keeping with local legal and regulatory requirements.

## Discussion

The idea to redirect immunity via bispecific antibodies is currently one of the most compelling concepts in cancer treatment. In the meantime, various bispecific antibody formats have entered clinical trials indicating their enormous therapeutic potential [22-24].

In the present phase I/II trial, the anti-CD3 x anti-CD20 trAb FBTA05 is applied in combination with DLI in patients with CD20-positive CLL, low- and high-grade NHL relapsed or refractory after allo-SCT. The primary goal of this combined FBTA05/DLI treatment approach is to further improve an already successful allogeneic DLI regime for patients with resistant B cell malignancies who relapsed after allo-SCT [25,26]. In addition, Riechelmann and co-workers showed that opsonization of autologous effector cells (i.e. peripheral blood mononuclear cells) with anti-EpCAM x anti-CD3 trAb catumaxomab led to beneficial results (i.e. tolerability, safety and response) in patients with intractable recurrent head and neck squamous cell carcinomas [27]. Based on these findings and anticipating our own preliminary clinical data from a small pilot study [16], the planned treatment schedule is designed to enhance the targeting of tumor cells by allogeneic T lymphocytes while reducing the risk of undesirable GVHD reactivity against normal host cells. Hence, FBTA05 may maximize GVL effects by simultaneously decreasing the incidence and severity of GVHD as already shown in preclinical models [28,29]. Of note, these studies about the enhancement of graft-versus-tumor effects and the reduction of GVHD by means of combined DLI/trAb application was thoroughly performed upon administration of C57 splenocytes with or without pretreatment of anti-EpCAM x anti-CD3 trAb BiLu in (BALB x C57BL/6) F_1_ H-2^d/b^ mice that were previously inoculated with a lethal dose of B16-EpCAM melanoma cells. Importantly, the C57 spleen cells were syngeneic to the B16-EpCAM tumor cells, but haploidentically mismatched to host cells. Treatment with BiLu protected recipient mice from the alloreactive C57 splenocytes, as GVHD-related death was observed in only 20% of mice whereas almost all mice inoculated with naive C57 splenocytes w/o BiLu pretreatment died of GVHD [29]. In total 50% of all treated mice were disease-free in this experimental settings. BiLu treatment w/o cell therapy also had a substantial anti-tumor effect, as a similar proportion of treated mice were disease-free under these conditions [29]. Thus, future trials could also address the feasibility to pass on DLI in relevant clinical settings. Here, this clinical study with a combined trAb/DLI treatment might provide further insights into the capacity of this therapeutic regime to deplete malignant B cells, activate the immune system and induce secondary cell-mediated immunity.

## Trial status

The study is currently recruiting patients.
